#### Experimental intervention

Patients undergoing open colorectal procedures and randomized to the experimental arm will have the full length of their incision covered with an NPIT device (Prevena Incision Management System, KCI, Inc., San Antonio, TX, USA) starting in the operating room right after closure of the skin incision (see Fig. 2). In the intervention group, the NPIT system should cover the surgical wound for a minimum of 5 days and a maximum of 7 days (till postoperative day 5–7; visit 2; see Table 2). If the NPIT system is removed prior to postoperative day 5–7 (event visit; see Table 2) the reasons must be documented and a new NPIT system has to be applied to ensure coverage of the wound for 5–7 days after the operation. The reasons for a definite removal of the NPIT system prior to postoperative day 5–7 must be documented and state whether there is a surgical site infection (the primary endpoint measure of the trial) or whether the NPIT system is not tolerated by the patient.

**Fig. 2 Fig2:**
[figure not shown]
Negative-pressure incision therapy wound device used in the Poniy trial. The sterile foam is placed on the skin incision immediately after skin closure and attached to the skin via the adhesive dressing. A fixed negative pressure of −75 mmHg to −125 mmHg is applied via the negative-pressure pump and the attached tubing. Wound secretions are collected in a canister, which is integrated in the pump

#### Control intervention

Incisions will be covered with standard sterile dressings postoperatively. Frequency of dressing changes depends on local practice.

### Risks

No additional risks for study patients are anticipated, since the safety and feasibility of the application of the NPIT device on postoperative abdominal wounds has been established in several previous studies. The NPIT device used in Poniy trial is CE (Conformité Européenne) certified. The surgical procedures carried out within Poniy are not affected by the trial.

### Outcome measures

The primary efficacy endpoint measure of the Poniy trial is the rate of surgical site infections within 30 days after the operation, according to CDC criteria, which constitute an internationally accepted standard definition [9] (Table 1). If the patient’s wound cannot be evaluated on postoperative day 30, a clinical evaluation according to the CDC criteria up to postoperative day 35 will be allowed.

The following outcome measures have been defined as secondary endpoint measures:Duration of hospital stay (in days);Rate of reoperation in both groups;Duration of postoperative antibiotic treatment in both groups within 30 days (in days);Duration of NPIT therapy (in days) in the interventional arm;Wound pain, as assessed by a visual analogue scale (graded from 1 to 10) in both groups;Rate of wound complications other than wound infections in both groups;Number of postoperative severe adverse events in both groups within 30 days.

### Data management

All required information collected during the trial will be entered in a case record form by the investigator or a designated representative. Documentation is expected to be completed as soon as possible after information has been collected. The investigator is responsible for the accuracy of the documentation and must ensure that all entries can be verified by source data. An explanation must be given for all missing data. Corrections in the case record form must be signed, dated and leave the corrected entry visible. The completed case record form must be reviewed, signed and dated by the investigator named in the trial protocol or by a designated sub-investigator. After a copy is made for retention at the trial centre, the original case record form is sent in a sealed envelope by certified mail to the Centre for Data Management at the Münchner Studienzentrum, a member of the Network of Coordinating Centres for Clinical Trials (Koordinierungszentren für Klinische Studien Network) at the Technische Universität München, Munich, Germany. Double data entry is performed by data management according to standard operating procedures predefined in the data management plan to ensure correct transfer of data from the case record form to the database (MACRO™ version 3, Microsoft SQL Datenbank, using Microsoft Internet Explorer version 6 or higher). Completeness, validity and plausibility of data are examined by validating programs as well as individual inspection and any queries generated as a consequence must be clarified by the investigator or designated sub-investigator. At the end of the trial, the principal investigator will retain the original case record forms.

### Monitoring

Monitoring of the trial data will be performed by an independent institution experienced in the monitoring of surgical trials (Koordinierungszentren für Klinische Studien Network) at the Münchner Studienzentrum. Monitoring will be carried out in accordance with ICH-GCP guidelines [37] and standard operating procedures of the Münchner Studienzentrum, to ensure patients’ safety and integrity of the clinical data, e.g., primary outcome measure in adherence to study protocol. All trial sites are activated with an initiation visit by the monitor or CHIR-Net coordinator, who will deliver and explain the investigator site file, discuss relevant issues and train trial personnel in study-specific interventions. Regular contact by phone or email with all participating centres will enable the CHIR-Net coordinator and the monitor to control study progression and adherence to the study protocol, and to discuss problems related to the study. Regular on-site monitoring visits are planned for all sites. Investigators must allow the monitor to look at all essential documents, support the monitor during visits and answer queries. All monitoring procedures will be predefined in a trial-specific monitoring manual. In addition, a GCP-trained flying study nurse employed by the CHIR-Net regional centre Munich will assist the trial sites with documentation and data collection if needed. Furthermore, close-out visits are planned for each centre.

### Safety evaluation and reporting of adverse events

An adverse event is defined as any untoward medical occurrence in a patient that does not necessarily have a causal relationship with the trial treatment and that occurs between inclusion of the patient and visit 6. The following exceptions are predefined in the study protocol and will not be recorded as adverse events: (1) occurrence of surgical site infection (the primary endpoint measure) is assessed as endpoint measure only (not as an adverse event); (2) any adverse event that is expected during the postoperative course or the underlying disease (e.g., pain, nausea, vomiting, hypertension, hypotension, imbalances of blood sugar or electrolytes or other laboratory values out of range) and that does not exceed grade I of the Dindo–Clavien classification of postoperative complications [38, 39] (Table 3). Assessment will be performed by the investigator or the designated sub-investigator.

**Table 3 Tab3:** Dindo–Clavien definition of postoperative complications [38]

Grade	Definition
I	Any deviation from the normal postoperative course without the need for pharmacological treatment or surgical, endoscopic or radiological intervention
	Allowed therapeutic regimens are: drugs as antiemetics, antipyretics, analgesics, diuretics, electrolytes and physiotherapy
	This grade also includes wound infections opened at the bedside
II	Requiring pharmacological treatment with drugs other than those allowed for grade I complications
	Blood transfusions and total parenteral nutrition are also included
III	Requiring surgical, endoscopic or radiological intervention
IIIa	Intervention, not under general anesthesia
IIIb	Intervention, under general anesthesia
IV	Life-threatening complication (including central nervous system complications)^a^ requiring intermediate care or intensive care unit management
IVa	Single organ dysfunction (including dialysis)
IVb	Multiorgan dysfunction
V	Death of a patient
Suffix ‘d’	If the patient suffers from a complication at the time of discharge (see examples in Table 1), the suffix ‘d’ (for ‘disability’) is added to the respective grade of complication. This label indicates the need for a follow-up to fully evaluate the complication.

^a^Brain haemorrhage, ischaemic stroke, subarachnoidal bleeding, but excluding transient ischaemic attacks

From the day the patient signs informed consent until the regular end of the trial (visit 6) or until premature withdrawal of the patient, all serious adverse events will be documented on a serious adverse event form, available in the investigator site file. A serious adverse event will be defined as an event that results in death, is immediately life-threatening, requires or prolongs hospitalization, or results in persistent or clinically important disability or incapacity, as judged by the investigator or designated sub-investigator. Serious adverse events will be classified by intensity (mild, moderate, severe), outcome (ongoing, recovered completely, recovered with sequelae, death, unknown) and causality (unrelated; possibly, probably or definitely related to trial intervention; not assessable). The assessment is based on clinical findings and needs to be made by the investigator or designated sub-investigator in the participating trial centre. Serious adverse events must be reported within 7 days after becoming known.

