### Randomization and blinding

Randomization and blinding will be performed with the help of sealed, opaque, individually numbered envelopes, restricted to choosing one at a time. The envelopes contain data sheets with information regarding the group allocation and the randomization number. Both are prefabricated by a biostatistician of the *Technische Universität München* (Munich, Germany). Randomization (visit 2, see Fig. 1) will be performed in the operation theatre at the end of surgery, after closure of the skin. This prevents potential bias by different methods of wound closure or wound irrigation. An interrupted skin closure must be performed with either sutures or staplers, according to local practice.

Randomization will be stratified by centre. To assure balanced group sizes, a block-wise randomization will be applied. Basic characteristics of the patient and day of randomization must be documented on the randomization sheets. Subsequently, randomization sheets must be dated, signed and stored away from the patient records and the trial documents, as well as the investigator site file, to ensure blinding. Patients, outcome assessors and the trial statistician will be blinded for the trial intervention. The outcome assessor (postoperative surgical site infection) will therefore neither be part of the surgical team that performs the trial intervention nor take part in the postoperative care of the patient and will have no access to the randomization sheets. Blinding of patients is not feasible, as the NPIT wound dressing system is different from the standard sterile dressing. However, the primary endpoint measure (whether or not there is surgical site infection according to the CDC definition, Table 1) cannot be influenced by the subjective assessment of the patient.

**Table 1 Tab1:** Definitions of abdominal surgical site infections classified according to the Centres for Disease Control and Prevention [9]

Superficial incisional surgical site infections	Deep incisional surgical site infections^a^	Organ or space surgical site infections
1. Infection occurs within 30 days after the operation, and	1. Infection occurs within 30 days after the operation, and	1. Infection occurs within 30 after the operation, and

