### Interventions

The schedule of trial interventions is presented in Table 2.

**Table 2 Tab2:** Study visits of the Poniy trial

Activity	Visit 1 (screening, inclusion)	Visit 2 (operation + randomization)	Visit 3 (postoperative day 5–7)	Visit 4 (postoperative day 9–11)	Visit 5 (discharge)	Visit 6 (postoperative day 30–35)	Optional visit (anytime between visits 2 and 6)
Inclusion and exclusion criteria	×						
Informed consent	×						
Medical history	×						
Physical examination	×						
Surgery		×					
Randomization		×					
Documentation of surgical site infection^a^			×^b^	×^b^	×^b^	×^b^	×^b^
Documentation of other wound complications^c^			×				×
Measurement of wound length			×				
Documentation of wound pain (visual analogue scale, 1–10)			×	×	×	×	×
Documentation of reoperation			×	×	×	×	×
Documentation of adverse or serious adverse events		×	×	×	×	×	×
Documentation of antibiotic-therapy			×	×	×	×	×

^a^By blinded wound assessor according to definition of US Centers for Disease Control and Prevention

^b^In case of surgical site infection, a microbiological swab according to local practice should be obtained for microbiological specification and antimicrobial testing

^c^Documented as ‘yes’ if blister formation and ‘no’ otherwise

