#### Safety analysis

For safety analysis, all adverse and serious adverse events will be analyzed via descriptive statistical methods. For comparisons of frequencies between groups, the chi-square test and, if appropriate, the Fisher exact test, will be used. Patients who have started visit 2 (operation) will be analyzed as treated.

Procedures for the statistical analysis of the primary and secondary endpoint measures will be conducted in line with the GCP-ICH E9 guideline [40]. For the statistical analysis, IBM SPSS Statistics version 21.0 will be used (IBM Corp., Armonk, NY). Statistical analysis will be performed by a group-allocation blinded statistician from the Institute for Medical Statistics and Epidemiology of the Technische Universität München.

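### The between-arm safety comparison takes in events that precede randomisation, and, separately, the secondary safety endpoint counts *severe* events where the protocol defines and collects *serious* ones

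*Protocol article*

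**What the plan says.** All references are to the protocol article.

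- **Collection window.** Under Safety evaluation and reporting of adverse events, an adverse event is one that "occurs between inclusion of the patient and visit 6". Serious events are documented "From the day the patient signs informed consent until the regular end of the trial (visit 6") or until withdrawal.
- **Visit schedule.** In Table 2 (Interventions), the row "Documentation of adverse or serious adverse events" is first ticked at visit 2, the operation and randomisation visit. It is not ticked at visit 1.
- **Randomisation.** Under Randomization and blinding, it "will be performed in the operation theatre at the end of surgery, after closure of the skin".
- **Analysis.** Under Safety analysis, "all adverse and serious adverse events will be analyzed via descriptive statistical methods". Frequencies are then compared between groups by chi-square or Fisher exact test. No limit on onset is given.
- **Named endpoint.** The last of the seven secondary measures under Outcome measures is "Number of postoperative severe adverse events in both groups within 30 days".
- **Serious and severe.** The safety evaluation section defines seriousness by consequence: "A serious adverse event will be defined as an event that results in death, is immediately life-threatening, requires or prolongs hospitalization", or lasting disability. It uses *severe* for something else: "Serious adverse events will be classified by intensity (mild, moderate, severe").

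**The concern.** There are two separate points, and they concern different analyses.

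First, the arms do not exist until the skin is closed. A complication during the operation cannot have been caused by a dressing that was not yet on the wound, and its risk is the same in both arms apart from chance. If such events are counted in the group comparison, they add the same background to each side and make any real difference look smaller. In a safety comparison that is the unhelpful direction, because it can hide harm. The Risks section anticipates no additional risk, and this comparison is what would test that expectation.

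Second, the endpoint and the data collection use different words, and the protocol gives each word its own meaning. *Serious* describes what an event leads to; *severe* is the top of three intensity grades given to serious events. The same data can therefore give two different counts for one named endpoint: all serious events, or only those graded severe.

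**Working it through.** **The plan's own figure.** The only computed figure is the primary-endpoint sample size. With 25% v 12.5%, two-sided 5% and 80% power:

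n = [1.960·√(2·0.1875·0.8125) + 0.842·√(0.25·0.75 + 0.125·0.875)]² / 0.125² = 152 per group (power 0.800).

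It reproduces, and neither point touches it. The plan states no adverse event rate and no power for safety.

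**Point 1, by timeline.**

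1. The definition of an adverse event opens at inclusion; for serious events it opens at consent.
2. Table 2 schedules the documentation only from visit 2. That does not match the start at inclusion, but it still covers the operation itself.
3. The Safety population section takes in everyone who started visit 2, so it too opens before allocation.
4. Allocation follows skin closure.
5. The Safety analysis section takes all events and tests frequencies between groups.

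Events between steps 1 and 4 therefore fall inside the comparison. Given Table 2, these are mainly intraoperative events.

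**Point 1, illustrated size (all rates assumed).** Let p_C and p_T be the proportions of patients with an event after randomisation. Let q be the proportion with an earlier event, equal in both arms and independent of later events. The proportion with any event is 1 − (1 − p)(1 − q), so the risk difference shrinks by the factor (1 − q). Power is for a two-sided 5% comparison at 170 per arm.

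| Assumed p_C v p_T | q | Any event, control v device | Risk ratio | Power |
|---|---|---|---|---|
| 20% v 30% | 0 | 20.0% v 30.0% | 1.50 | 0.568 |
| | 5% | 24.0% v 33.5% | 1.40 | 0.490 |
| | 10% | 28.0% v 37.0% | 1.32 | 0.425 |
| | 20% | 36.0% v 44.0% | 1.22 | 0.324 |
| 10% v 20% | 0 | 10.0% v 20.0% | 2.00 | 0.735 |
| | 5% | 14.5% v 24.0% | 1.66 | 0.604 |
| | 10% | 19.0% v 28.0% | 1.47 | 0.499 |
| | 20% | 28.0% v 36.0% | 1.29 | 0.352 |

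Example: 1 − 0.95·0.70 = 0.335 and 1 − 0.95·0.80 = 0.240; 0.335/0.240 = 1.40.

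**Point 2, by definition.** Take a complication that prolongs the hospital stay and is graded moderate. It is serious under the protocol's definition. It counts if the endpoint means *serious* and does not count if it means *severe*. A non-serious event has no intensity grade stated in the article. The severe count can therefore equal the serious count or be smaller, never larger.

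**Point 2, illustrated size (assumed).** If serious events affect 10% v 20% and a share s of these patients have one graded severe, the endpoint rates are s·10% v s·20%:

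- s = 25%: 2.5% v 5%, power 0.227
- s = 50%: 5% v 10%, power 0.417
- s = 75%: 7.5% v 15%, power 0.591
- s = 100%: 10% v 20%, power 0.735

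**The case against.** Collecting events from consent is normal and is not an error. The Safety analysis section is mainly descriptive, and the rule on which events enter a table is often left to the analysis plan, which is not shown and could narrow the window. Serious events also carry a causality rating that includes *unrelated*. All of this is fair. What stands is that the section does not merely leave the window open: it says all events and attaches group tests. The causality rating is not used to select events for those tests.

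The rates in the illustration are assumed, and nothing in the article shows how common intraoperative events that meet its definitions would be. This stands in full: the tables show direction and mechanism only.

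A reader might infer three stronger things that the article does not support.

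- *That the named secondary endpoint is also contaminated by earlier events.* It is limited to postoperative events, and randomisation takes place at the end of surgery. No single analysis has both faults.
- *That the endpoint's 30 days contradicts collection up to visit 6 (day 30 to 35).* Counting to day 30 from data collected a little longer is an ordinary subset.
- *That preoperative events enter on a large scale.* Table 2 schedules no adverse event documentation at visit 1.

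The mismatch of *severe* and *serious* can be called a slip of wording in the last of seven secondary endpoints. It is a small matter, but because the protocol itself gives *severe* a separate meaning, the text does not settle which count is intended.

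**Conclusion.** Both points hold, each for its own analysis.

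1. As written, the between-arm comparison of all adverse and serious adverse events includes events before randomisation, mainly intraoperative ones, and is diluted toward no difference. The size cannot be given, because the article states no event rates. With arms analysed as randomised, the effect is noise and lost sensitivity, not systematic bias. That condition matters because the Safety population section says as randomised and the Safety analysis section says as treated, a separate conflict that also needs settling.
2. The secondary safety endpoint, read literally, leaves out serious events graded mild or moderate. How many is unknown, since it depends on the share graded severe.

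Neither point affects the primary endpoint, the sample size or any decision rule.

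**What to change.** **Safety analysis section.** Keep collecting from consent. Limit the between-arm tests to events with onset after randomisation, and list earlier events separately without a group test. Add a before/after-randomisation flag or the onset time to the event form. A date alone is not enough: the operation and randomisation share one theatre session, so a date cannot separate an intraoperative event from one in the first hours under the dressing. Bring the first tick in Table 2 into line with the stated start of collection.

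**Outcome measures section.** Replace *severe* with *serious*, as defined in the safety evaluation section.

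**Cost.** A few words in each section and one extra field on the event form. The flag has to be completed at the time of the event, so it is best added before recruitment starts.

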### Statistical methods

#### Sample size calculation

Sample size calculation is based on the primary endpoint measure (whether or not there is surgical site infection, according to CDC) within 30 days post operation [9] and was conducted by using nQuery Advisor® software version 7.0 (Statistical Solutions Ltd, Cork, Ireland). Based on the assumption that the percentage of patients developing postoperative wound infections in a surgical population undergoing open colorectal surgery is approximately 25 % for the control group (based on results from previous randomized controlled trials in abdominal surgery [14, 15, 17]) and can be reduced to 12.5 % in the experimental intervention arm, a group sample size of 152 patients would need to be compared using the chi-square test, to achieve 80 % power in detecting this difference in surgical site infection rate at a two-sided level of significance of 5 %. Under the assumption of a drop-out rate of up to 15 %, a total of 340 patients (170 per group) need to be enrolled in the study. Owing to the broad inclusion criteria and the limited number of exclusion criteria, the limited study time per patient (30 days), as well as the comprehensible nature of the trial, no more than 100 patients are expected to fail the screening process. Therefore, the total number of patients needed for screening is 440 (Fig. 1).

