**Methods/Design:**

The aim is to investigate whether the postoperative application of a negative-pressure incision therapy device for 5–7 days reduces the rate of surgical site infections following open elective colorectal surgery by 50 %. This is a randomized, controlled, observer-blinded multicentre clinical trial with two parallel study groups. The primary outcome measure will be the rate of surgical site infections within 30 days postoperatively. Surgical site infections are defined according to criteria of the US Centers for Disease Control and Prevention. Statistical analysis of the primary endpoint measure will be based on the intention-to-treat population. The global level of significance is set at 5 % (two-sided) and the sample size (*n* = 170 per group) is determined to assure a power of 80 %.

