### Sample size

A total of 152 patients will be analyzed per group. Given an estimated drop-out rate of approximately 10 %, 340 patients will be randomized to the two treatment arms.

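### Enrolling 340 patients does not cover the stated drop-out of up to 15% (that needs 358), and the protocol gives two drop-out rates, 10% and 15%, for the same 340

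*Protocol article*

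**What the plan says.** The protocol article sizes the trial in two places.

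- **Statistical methods, Sample size calculation.** The control infection rate in patients "undergoing open colorectal surgery is approximately 25" per cent, and it is assumed that this "can be reduced to 12.5" per cent with the device. At a "two-sided level of significance of 5" per cent and 80% power, "a group sample size of 152 patients would need to be compared using the chi-square test". The allowance for loss follows: "Under the assumption of a drop-out rate of up to 15" per cent, "a total of 340 patients (170 per group) need to be enrolled in the study".
- **Methods/Design, Sample size.** The same 152 analysed per group and the same 340 randomized appear, but with a different allowance: "Given an estimated drop-out rate of approximately 10" per cent.

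The abstract gives no drop-out rate. It says that 170 per group "is determined to assure a power of 80" per cent.

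**The concern.** One calculation has one starting figure (152 per group) and one result (340), but two different inputs between them. At most one of the two drop-out rates can be the one that produced 340, and nothing in the article reconciles them.

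The drop-out allowance sets the enrolment target and marks the loss beyond which the trial is underpowered. Anyone monitoring the trial against the Statistical methods section would take 15% loss as still within plan. If the true margin is smaller, the 80% power in the abstract is not secured at a loss the protocol says it allows for.

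**Working it through.** **Inputs, all from the Sample size calculation section:** control rate 0.25, device rate 0.125, two-sided 5%, power 80%, chi-square test, equal groups, 152 evaluable and 170 enrolled per group, drop-out up to 15%. The Sample size section under Methods/Design supplies the other rate, about 10%.

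**Step 1: reproduce 152.** For the chi-square test without continuity correction, with mean rate p = (0.25 + 0.125)/2 = 0.1875:

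n = [1.960 × √(2 × 0.1875 × 0.8125) + 0.842 × √(0.25 × 0.75 + 0.125 × 0.875)]² / 0.125² = 151.9, rounded up to 152 per group.

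Power at 152 per group is 80.0%. The base figure is correct, so the problem lies only in the allowance for loss.

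**Step 2: inflate for loss, n/(1 − d).**

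| Drop-out d | Per group | Total | Against 340 |
|---|---|---|---|
| 10% | 152/0.90 = 168.9, so 169 | 338 | agrees, rounded up |
| 15% | 152/0.85 = 178.8, so 179 | 358 | 18 short |

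The common shortcut of multiplying by 1 + d does not give 340 at 15% either: 152 × 1.15 = 174.8, so 175 per group and 350 in total.

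**Step 3: the loss that 340 can absorb.** 1 − 152/170 = 10.6%.

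**Step 4: power if loss occurs, counting only evaluable patients** (normal approximation, 25% v 12.5%):

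- 10% loss: 170 × 0.90 = 153 per group, power 80.3%.
- 15% loss: 170 × 0.85 = 144.5 per group, power 77.9% at 144 and 78.1% at 145.

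**Step 5: the same losses under the protocol's missing-data rule.** The Intention-to-treat population section keeps patients lost to follow-up and counts them as not infected. Loss then lowers both rates instead of reducing n. Assume that all loss is of this kind and equal in both arms:

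- 10% loss: rates 0.25 × 0.90 = 22.5% and 0.125 × 0.90 = 11.25%; power at 170 per group about 79.4%.
- 15% loss: rates 0.25 × 0.85 = 21.25% and 0.125 × 0.85 = 10.6%; power at 170 per group about 76.5%.
- 15% loss with 179 per group: power about 78.7%.

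**The case against.** The strongest reply is that 340 is right and only the 15% is a slip. The 340 agrees with the 10% in the Methods/Design section, and 170 per group is used consistently. On that reading this is a text inconsistency and not an under-enrolled trial. That is probably so, although the documents do not show which rate was intended. It does not remove the error, because the sentence with 15% is wrong as it stands. Taking 10% as the expectation and 15% as a ceiling does not help either: 340 is given as the number needed at up to 15%, so it should suffice at 15%, and it does not.

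A second reply is that the 78% does not describe the primary analysis, which keeps lost patients in the intention-to-treat population. This is correct as far as it goes. The 78% is a complete-case figure, and it follows the protocol's own framing of 152 analysed per group. The intention-to-treat rule gives a lower figure at 15% (about 76.5% under the assumption in Step 5), so it does not rescue the plan. It does mean that any restated power should name the population it refers to, and that 358 restores 80% only for complete cases.

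Two smaller points also stand. The abstract carries no drop-out rate, so it needs changing only if 15% is kept. The consequence is modest: about 2 percentage points of complete-case power, and only if loss reaches the ceiling. The endpoint and the planned test are unaffected.

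**Conclusion.** The concern holds. The two sections attach different drop-out rates to the same 152 and the same 340, and the arithmetic supports only the rate of about 10%. At the stated 15%, enrolment is 18 patients short of the required 358, and complete-case power is about 78% instead of 80%. The tolerance for loss ends at 10.6%.

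The 78% rests on the protocol's assumed rates, equal loss in both arms, loss unrelated to infection, and removal of lost patients from the comparison. At the 10% in the Methods/Design section, complete-case power is 80.3% and the plan is consistent.

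**What to change.** Use one drop-out rate in both sections. The simplest correction is to change the Sample size calculation section to a drop-out rate of about 10%, adding that at most 10.6% loss leaves 152 evaluable patients per group, and to keep 340. The abstract can then stay as it is.

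If the sponsor wants to keep 15%, both sections should say so and state that 340 patients then give about 78% power for the complete-case comparison. The 80% in the abstract should be amended to match.

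Either option is a change of wording with no extra patients. The cost is that the stated loss tolerance or the stated power becomes slightly less favourable.

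Raising enrolment to 358 is possible but not required. It would add 18 patients, move the screening figure from 440 to 458 (358 + the 100 expected screening failures), and secure 80% power at 15% loss only for complete cases.
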